### Sample size

The sample size was calculated to compare two proportions with two-sample noninferiority or superiority. According to Muñoz et al., median blood loss was 2000 ml in parturients with PA during delivery [23]. The study of Panici et al. showed that median blood loss was 950 ml in parturients with AABO at cesarean section [24]. Considering a difference in volume of bleeding of 1000 ml with a standard deviation of 355 ml [13] in two treatment groups, a difference of 800 ml between two treatment groups is considered to be clinically important. Assuming the difference between two groups at a 2.5% significance level and a power of 0.90, 67 patients in each group are required for a comparison within the groups. Considering an estimated 20% dropout rate, 85 patients in each group for a total of 170 patients will be included in this study.

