### Randomization, allocation concealment, and blinding

Subjects who meet the eligibility criteria will be randomly assigned to either the traditional treatment group or the interventional treatment group. Group assignments are generated using a computer algorithm (Winpepi version 11) that allocates patients in equal numbers to both groups. The randomization list will be sealed in sequentially numbered opaque envelopes, which will be stored in a double-locked cabinet. Randomization is implemented by a research assistant who is not involved in recruitment. After random assignment, the envelopes will again be stored separately in a double-locked cabinet. Allocation concealment will not be broken until the trial is complete.

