### Data collection

#### Primary outcome

The primary outcome is estimated blood loss (EBL). EBL is measured with reference to the collected blood in the suction bottle in the operating room and to the weight of the surgical swabs, excluding the volume of amniotic fluid.

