### Statistics

An intention-to-treat analysis will be performed to compare all primary and secondary outcomes in the future study. Continuous variables will be described as means ± standard deviation (SD). Categorical variables will be described as percentages. Demographic data, blood transfusion volume, operating time, length of stay in the ICU, total hospital stay, and EBL will be analyzed by Student’s *t* test to compare the two methods. The occurrence of CH during delivery will be compared by the chi-square test. The neonate Apgar scores will be analyzed using the Mann-Whitney *U* test.

The statistical analyses will be carried out with SPSS software (SPSS, Inc., Chicago, IL, USA). The statistical significance will be considered with a two-tailed *P* value <0.05 and a one-tailed *P* value <0.025.

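### The 67 per group fits a test of superiority by 800 ml (mislabelled as a comparison of proportions), but the Statistics section plans a t test with no margin, so the stated 90% power does not describe that test

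*Protocol article*

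**What the plan says.** All references are to the protocol article.

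- Primary outcome: "The primary outcome is estimated blood loss (EBL"), a volume in ml.
- Sample size, method: "The sample size was calculated to compare two proportions with two-sample noninferiority or superiority".
- Sample size, inputs: "Considering a difference in volume of bleeding of 1000 ml with a standard deviation of 355 ml", followed by "a difference of 800 ml between two treatment groups is considered to be clinically important".
- Sample size, result: "at a 2.5% significance level and a power of 0.90, 67 patients in each group are required". The same section then states: "Considering an estimated 20% dropout rate, 85 patients in each group for a total of 170 patients".
- Statistics: "length of stay in the ICU, total hospital stay, and EBL will be analyzed by Student"'s t test, to compare the two methods. Significance is set at two-tailed 0.05 and one-tailed 0.025. The section gives no margin, no shifted null value and no confidence limit to be set against 800 ml.
- The Abstract and Trial design speak only of testing superiority.

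**The concern.** There are two faults, one plain and one that shows only in the arithmetic.

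The plain one is the label. No proportion appears among the inputs; they are a difference in ml and an SD. Naming noninferiority or superiority as alternatives also leaves the hypothesis open, although the rest of the article commits to superiority.

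The second is that the sample size and the analysis appear to belong to different hypotheses. The number 67 fits a test of whether the reduction exceeds 800 ml. A Student's t test with no margin asks, by default, whether there is any difference. If both sections stand, the stated power does not describe the primary test. The protocol also does not say whether a significant but modest reduction in blood loss counts as success, and that should be settled before any data are seen.

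**Working it through.** **Inputs.** From Sample size: expected difference 1000 ml, SD 355 ml, clinically important difference 800 ml, significance level 2.5% (sidedness not stated), power 0.90. From the randomization section: 1:1 allocation ("allocates patients in equal numbers to both groups"). From Statistics: Student's t test, two-tailed 0.05 or one-tailed 0.025.

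**1. Reproducing the 67.** For two means with 800 ml as the margin, by the normal approximation:

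n = 2 × (z(0.975) + z(0.90))² × SD² / (1000 − 800)²
= 2 × (1.960 + 1.282)² × 355² / 200²
= 66.2, rounded up to **67**.

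Power at n = 67 is 90.3% by the same approximation. The noncentral t gives n = 68.

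**2. Other readings of the same inputs.**

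| Reading | n per group |
|---|---|
| Margin 800 ml, 2.5% two-sided | 79 |
| Margin 800 ml, 5% one-sided | 54 |
| Null of zero, effect 800 ml, two-sided 5% | 5 (6 by noncentral t) |
| Null of zero, effect 1000 ml, two-sided 5% | 3 (4 by noncentral t) |
| Two proportions | cannot be run; no proportions given |

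A zero-null test for an effect of 200 ml also gives 66.2, because 200 is the only difference that enters the formula. The section does not state an effect of 200 ml; it arises only as 1000 − 800.

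**3. Dropout step.** 67 / 0.8 = 83.75, so 84 against the stated 85 (68 / 0.8 = 85 exactly). This is immaterial.

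**4. What the planned t test does at 67 per group and SD 355 ml.**

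- Standard error of the difference: 355 × √(2/67) = 61.3 ml.
- Smallest significant observed difference: t(0.975, 132 df) × 61.3 = 1.978 × 61.3 = about 121 ml.
- Observed difference needed by a test against 800 ml: 800 + 121 = about 921 ml.
- True difference detected with 90% power by the zero-null test: (1.960 + 1.282) × 61.3 = about 199 ml.
- Power of the zero-null test at a true 800 or 1000 ml: above 99.9%.

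With all 85 per group, the two cut-offs are about 108 and 908 ml.

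**5. Dependence on the SD at 67 per group.** SDs other than 355 ml are assumptions. They are worth showing because the Background cites a median loss of about 2000 ml, with more than 10,000 ml in 10% of cases in some institutions.

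- Zero-null test, two-sided 5%, by noncentral t: 90% power for 800 ml holds up to an SD of about 1418 ml, and for 1000 ml up to about 1773 ml.
- Test against 800 ml with a true difference of 1000 ml: about 90% power at SD 355 ml and about 21% at SD 1000 ml.

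**The case against.** **The margin is inferred.** The text calls 800 ml clinically important and never calls it a margin or a null value. Statistics does not write out a null of zero either; a t test can be run against a shifted null, and the one-tailed 0.025 there matches the one-sided 2.5% behind the 67. This stands as a limit on certainty. A reader might infer that the trial will definitely run the wrong test, but the document does not go that far; it supports only that Statistics, as written, names an ordinary t test with no margin. If 800 ml is not a margin, the 67 does not follow from the stated inputs and Sample size still needs correcting. A separate analysis plan might supply the null value, but it could not make the proportions label right.

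**There is no power shortfall on the plan's inputs.** This also stands. A reader might infer that the trial is underpowered, but at SD 355 ml the zero-null t test has far more power than it needs.

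**Results between 121 and 921 ml are not contradictory.** Correct: a reduction greater than zero and a reduction not shown to exceed 800 ml are compatible findings. What differs is whether the trial counts as a success. Those bounds also hold only at SD 355 ml.

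**Low success at a true 800 ml is no defect.** A test against 800 ml would succeed 2.5% of the time if the true difference were exactly 800 ml. That is its type I error, and it should not be counted as a fault.

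**Conclusion.** The point holds as an inconsistency between two sections plus a wrong label. The sample size was not calculated for proportions. From the stated inputs, 67 per group arises only with 800 ml as a superiority margin, and the t test in Statistics carries no such margin. The 90% power therefore does not belong to the planned primary test, whose power on the same inputs is above 99.9% at 800 ml. At SD 355 ml and 67 per group, any observed difference between about 121 and 921 ml meets one section's criterion and not the other's.

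This rests on two readings: that 800 ml is a margin, inferred from the arithmetic, and that a t test without a margin has a null of zero. The choice between them matters because the two tests respond very differently to an SD larger than 355 ml. It should be corrected before recruitment, which had not begun at publication.

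**What to change.** In Sample size, replace the reference to proportions and to noninferiority or superiority with two means, superiority. Then use one null hypothesis in Sample size and Statistics:

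- **(a) Keep the zero-difference t test, two-sided 5%.** Restate the power of 67 evaluable patients per group for this test, and state and justify the SD it relies on. The limits of about 1418 ml (for 800 ml) and 1773 ml (for 1000 ml) show how much room there is; they do not replace a justified SD. Say that significance then shows a reduction, not a reduction above 800 ml.
- **(b) If superiority by 800 ml is intended,** write that test into Statistics: success if the lower limit of the two-sided 95% confidence interval for the reduction exceeds 800 ml. State that the 90% power holds only if the SD is about 355 ml, and falls to about 21% if the SD is assumed to be 1000 ml.

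The cost is wording in two paragraphs. No extra patients are needed to make the sections consistent. The price is a narrower claim under (a), or power that is sensitive to the SD under (b).

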### Statistics

An intention-to-treat analysis will be performed to compare all primary and secondary outcomes in the future study. Continuous variables will be described as means ± standard deviation (SD). Categorical variables will be described as percentages. Demographic data, blood transfusion volume, operating time, length of stay in the ICU, total hospital stay, and EBL will be analyzed by Student’s *t* test to compare the two methods. The occurrence of CH during delivery will be compared by the chi-square test. The neonate Apgar scores will be analyzed using the Mann-Whitney *U* test.

The statistical analyses will be carried out with SPSS software (SPSS, Inc., Chicago, IL, USA). The statistical significance will be considered with a two-tailed *P* value <0.05 and a one-tailed *P* value <0.025.

### Data processing and security monitoring

All data will be collected in accordance with the approved agreement and recorded separately. The Information Board (data monitoring committee, DMC) is composed of two senior professors, an epidemiologist, a biostatistics expert, and an ethical expert without any conflict of interest. Weekly meetings and public meetings are held to ensure data availability and scientific integrity while protecting patient safety. The main goals are to ensure the safety and interests of the subjects, the integrity and credibility of the study, and timely and accurate feedback to the clinical research related to the field. All treatment-related adverse events will be observed and reported by participants at each visit. In the event of serious adverse reactions, detailed reports will be drafted assessed on the basis of the protocol. Data and safety monitoring will be conducted regularly during the study period.

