## Background

Placenta accreta (PA), a kind of morbidly adherent placenta, involves an absence of decidua basalis; the placenta always adheres to the underlying myometrium [1]. This morbidly obstetric condition is a severe complication during delivery. It is closely linked with massive hemorrhage, which could endanger the lives of both mother and baby [2, 3]. In patients with PA, median intraoperative blood loss is about 2000 ml during delivery, and in 10% of the cases it has been more than 10,000 ml in some institutions [4, 5]. Multiple pathophysiological conditions are involved in massive hemorrhage from patients with PA during cesarean section, including pelvic viscera injury to the bladder, ureter, bowel, or other organs during the surgery. When massive hemorrhage cannot be effectively controlled, multisystem organ failure (MOF) and disseminated intravascular coagulation (DIC) will follow [6]. Therefore, placenta accreta poses a serious threat to the safety of the mother.

However, in recent years, the incidence of PA has risen with the increasing rate of cesarean deliveries [7]. According to a World Health Organization (WHO) report, China has become the country with the highest rate of cesarean sections, up to 68%. China will face a big challenge with its two-child family policy initiation. In America, the cesarean delivery rate will be 56.2% if the cesarean rate continues to grow as it has in the past, and there will be 6236 patients with placenta previa, 4504 patients with placenta accreta, and 130 maternal deaths annually [8]. Therefore, studies evaluating the effects of different perioperative management approaches based on different modalities in the treatment of placenta accreta are necessary.

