In the traditional method, hysterectomy following cesarean section is usually indicated as the treatment option in patients with morbidly adherent placenta. This treatment reduces maternal morbidity, but it results in infertility [9]. To minimize intraoperative hemorrhage and facilitate surgery, some novel treatment options have been described, including proximal ligation of the internal iliac artery or uterine artery and vascular balloon catheters placed in the iliac artery, uterine artery, or even the abdominal aorta [10]. Among the numerous treatment measures, prophylactic balloon occlusion of the abdominal aorta seems to be more advantageous than others [11, 12]. Recently, a large-sample retrospective study from our single center also shows that prophylactic abdominal aortic balloon occlusion (AABO) has a promising future [13, 14]. These retrospective studies strongly suggest that we need an adequately powered prospective study to demonstrate the benefits and risks. Thus, the primary aim of the study is to investigate the benefits and risks of AABO in combination with cesarean section for PA.

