### Trial interventions

All patients will receive the standard multidisciplinary team service (including the senior obstetrician, gynecologist, anesthesiologist, neonatology teams, urologist, imaging doctor, and adequate number of blood units in the operating room). The antepartum diagnosis of PA is made clinically, based on the pelvic ultrasound or MRI. Pregnant woman with PA diagnosed by ultrasound or MRI will be recruited in this study. In both groups, pregnant woman will undergo the standard protocol, as described previously [14]. Considering the risk of massive bleeding complicated by profound hypotension and coagulopathy, we choose general anesthesia for all patients with PA [17, 18]. Endotracheal intubation is performed with the use of a rapid sequence induction (RSI) technique [19, 20]. We monitor invasive arterial blood pressure (ABP), electrocardiogram (ECG), SPO_2_, PetCO_2_, temperature (T), arterial blood gas (ABG), and thrombelastograph (TEG) of the patients during the operation. After fetal delivery and umbilical cord clamping, according to the PA location and depth, patients are given local excision of the uterine wall, placenta evacuation, partial cystectomy, and bladder repair. 20 U of oxytocin and 250 μg of tromethamine are injected in the myometrium.

In the traditional group, patients are given a cesarean section without AABO. In this group, conservative treatments for PA, including oversewing of the placental bed, a uterine tamponade, and bilateral uterine artery, ligation are used. Hysterectomy is performed when massive hemorrhage cannot be controlled.

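### The primary aim covers risks, but no complication outcome applies to both arms and the adverse-event rule filters on attribution, so the comparison of complications is incomplete and open to bias

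*Protocol article*

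**What the plan says.** The Background of the protocol article states that "the primary aim of the study is to investigate the benefits and risks of AABO in combination with cesarean section for PA". The abstract's Discussion likewise expects strong evidence on both benefits and risks.

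Three parts of the article bear on how risk is measured:

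- **Outcome list (Secondary outcomes).** The only item that names complications is tied to balloon occlusion: vascular aneurysm, dissection or rupture, and arterial embolism. The rest are hysterectomy, transfusion volume, Apgar scores, operating time, balloon data, and ICU and hospital stay.
- **Control treatment (Trial interventions).** "In the traditional group, patients are given a cesarean section without AABO"
- **Adverse events (Data processing and security monitoring).** "All treatment-related adverse events will be observed and reported by participants at each visit". The same section adds "In the event of serious adverse reactions, detailed reports will be drafted assessed on the basis of the protocol" and provides for a data monitoring committee.

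The Statistics section promises an intention-to-treat comparison of every primary and secondary outcome. It names tests for some of them: "The occurrence of CH during delivery will be compared by the chi-square test", and "Demographic data, blood transfusion volume, operating time, length of stay in the ICU, total hospital stay, and EBL will be analyzed by Student’s" *t* test. Apgar scores get a Mann-Whitney test.

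The Background also describes what goes wrong in surgery for this condition, "including pelvic viscera injury to the bladder, ureter, bowel, or other organs during the surgery", and then names multi-organ failure and DIC. The Trial interventions section names lower-limb venous thrombosis as something to be prevented.

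**The concern.** A randomised trial measures risk well when the same events are sought in the same way in both arms. Here the one complication outcome belongs to the device, so it yields a count in the AABO arm with nothing to set beside it. The events that could occur in either arm are left to an adverse-event rule with two weaknesses: someone must first judge the event to be caused by treatment, and the participant is the named reporter.

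What is at stake cuts both ways. If AABO reduces bleeding, fewer cases of DIC or organ injury could be among its main clinical gains. If it causes thrombosis or organ damage, that is its main cost. As written, the plan fixes no common measurement of either.

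**Working it through.** **1. The plan's own figure, for reference.** The sample size rests on blood loss and is not in dispute here. Inputs from the Sample size section are an expected difference of 1000 ml, a clinically important difference of 800 ml, SD 355 ml, 2.5% significance and power 0.90. Reading the 800 ml as a superiority margin, with a one-sided test:

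n = 2 × (1.960 + 1.282)² × 355² / (1000 − 800)² = 2 × 10.51 × 3.151 ≈ 66.2, so 67 per group, as stated.

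Allowing for 20% dropout, 67 / 0.8 = 83.75, so 84 against the stated 85. No complication rate enters, so nothing proposed below changes it.

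**2. Which harms have a like-for-like comparison?**

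| Harm | Where the article names it | Listed outcome? | Comparable between arms? |
|---|---|---|---|
| Hysterectomy | Secondary outcomes | Yes | Yes, chi-square |
| Transfusion volume, ICU stay, hospital stay | Secondary outcomes | Yes | Yes, *t* test |
| Apgar scores | Secondary outcomes | Yes | Yes, Mann-Whitney |
| Balloon complications | Secondary outcomes | Yes | No, there is no balloon in the control arm |
| Bladder, ureter or bowel injury | Background | No | Only through the adverse-event rule |
| DIC, multi-organ failure | Background | No | Only through the adverse-event rule |
| Lower-limb venous thrombosis | Trial interventions | No | Only through the adverse-event rule |

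**3. What the adverse-event rule does to the last three rows.** Let p be the true rate of an event, equal in both arms, and let a₁ and a₀ be the chances that such an event is judged treatment-related in the AABO and control arms. The recorded rates are p·a₁ and p·a₀, and the recorded difference is p(a₁ − a₀). This is not zero unless attribution works identically in both arms. The team treating the patient cannot be unaware of a balloon placed by radiologists in a hybrid room, and DIC or a ureteric injury can plausibly be ascribed either to the disease or to the procedure. The direction and size of (a₁ − a₀) cannot be derived from the article.

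**4. How precise would a common list be?** The article gives no complication rates, so the rates here are assumptions. With 85 per arm and the same rate p in both, the 95% half-width of the risk difference is 1.96 × √(2p(1 − p)/85):

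- p = 5%: 1.96 × 0.0334 = 6.6 percentage points
- p = 10%: 1.96 × 0.0460 = 9.0 percentage points
- p = 20%: 1.96 × 0.0614 = 12.0 percentage points

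Power of a two-sided 5% test is Φ{[|p₁ − p₀| − 1.96√(2p̄(1 − p̄)/85)] / √([p₀(1 − p₀) + p₁(1 − p₁)]/85)}, where p̄ is the mean of p₀ and p₁. It gives 0.33 for 1% v 5%, 0.59 for 5% v 15%, and 0.85 for 5% v 20%. Only large differences would be detected, so the aim should be estimation with intervals.

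**The case against.** The strongest reply is that harm is already compared. Hysterectomy, which the abstract calls the most important secondary outcome, costs the patient her fertility and is itself serious morbidity. It is tested between randomised arms, as are transfusion volume, ICU stay, hospital stay and Apgar scores. This stands. A reader might infer that the trial allows no randomised comparison of harm, or that the control arm contributes nothing; the Secondary outcomes and Statistics sections contradict that. What remains is that these measures do not identify organ injury, DIC, organ failure or thrombosis.

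A reader might also infer that the trial has no visits at which events could be reported. The article does not support that. It places the SPIRIT figure in an additional file that is not shown, and a condensed article may leave a visit schedule to the full protocol. Only the narrower statement is safe: the text at hand defines no visits.

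On the adverse-event sentence, three points are fair. Events are to be observed as well as reported, treatment-related can cover either arm's treatment, and general anaesthesia does not stop a patient reporting later. The article also does not say who judges attribution. Serious-reaction reports and committee oversight exist too. None of this removes the attribution filter or creates an outcome that is collected identically in both arms.

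Finally, rare-event arithmetic is tempting here. With no events in 85 patients the exact two-sided 95% upper limit is 1 − 0.025^(1/85) = 4.2%, and an event with an assumed rate of 1% would be missed with probability 0.99^85 = 0.43. Both are right, but they describe the size of one arm. They would be the same after the fix and do not measure this defect.

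**Conclusion.** The concern holds in a limited form. The primary aim includes risk, the only named complication outcome has no control rate, and the stated adverse-event rule selects on attribution. Four kinds of complication that the article itself names are therefore not outcomes, and their comparison between arms would be incomplete and open to attribution bias. This goes beyond missing detail, because the outcome list and the reporting rule are both stated, and an analysis plan cannot recover events that were never collected.

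The size of any bias cannot be given: the article supplies neither complication rates nor attribution practice. The conclusion assumes that the article's outcome list is the trial's list, and that those judging attribution would know the arm. The comparisons of blood loss, hysterectomy and the other listed shared outcomes are unaffected. The change should be made, but the primary analysis does not depend on it.

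**What to change.** 1. **Data processing and security monitoring.** Replace the adverse-event sentence with: *Study staff record all adverse events in both arms, regardless of attribution, from randomisation to discharge.* Attribution may still be noted as an extra field.
2. **Secondary outcomes.** Add one maternal and surgical complication list, defined and collected identically in both arms: unintended organ injury, DIC, organ failure, limb arterial or venous thromboembolism, re-operation, and death.
3. **Statistics.** Report the list by randomised arm, as risk differences with 95% confidence intervals.
4. **Keep separate and descriptive:**
   - embolisation, because the article describes supplementary embolisation after completion angiography only for the AABO arm;
   - planned bladder resection or repair, because it is among the procedures described for all patients and is not an injury;
   - balloon-specific complications, with an exact interval. A limb arterial embolism in an AABO patient would appear here and also count in the common list.

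The cost is a short addition to the case form, completed from hospital records, and the staff time to do so, which the article does not let us quantify. Intervals for rare events will be wide, and events after discharge will be missed. The sample size does not change.
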